### Primary and secondary outcome measures

The primary outcome for this study will be changes in proximal femur and lumbar spine aBMD. Secondary outcomes will comprise: changes in 4% and 66% tibial and radial vBMD, bone structure and strength, total body and regional body composition, muscle strength, functional capacity, cardiometabolic health, inflammatory biomarkers, HR-QoL and cognitive function.

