The Berg Balance Scale is an overall measure of balance including both dynamic and static components [75]. The test rates participants on 14 different tasks on an ordinal scale ranging from zero (unable to perform the task) to 4 (performs the task independently). Assessments include variations of sitting, standing, reaching, leaning, turning and stepping. The scores of the 14 tasks are summed to produce a total score ranging from 0 to 56 points. Higher scores indicate better performance. This test was observed to have an interrater and test-retest ICC of 0.98 and 0.97, respectively, in a sample of adults aged 65 years and over [75].

The 4-m usual walk is a measure of gait speed [76]. Participants will be instructed to walk at a usual pace between two cones 8 m apart (2-m acceleration zone, 4-m timed zone and 2-m deceleration zone). Time will be recorded when the participant’s front foot enters the timed zone and stopped when their front foot exits the timed zone. The time (to the nearest ms) to complete the timed zone was recorded with a stopwatch. This method has an ICC of 0.96 within our laboratory.

The 400-m walk test provides an estimate of cardiorespiratory fitness [77]. Participants will be instructed to walk as fast as possible between two cones placed 20 m apart (turning when they approach each cone). The time (to the nearest ms) taken to complete 10 laps (400 m) will be recorded. This test was observed to have a test-retest ICC of 0.95 in a sample of middle-aged women [78].

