#### Cognitive function

Previous research has shown that ADT use is associated with cognitive decline, particularly in the domains of verbal memory, visuomotor function, attention and executive function [80]. Thus, this study will include a number of established and valid cognitive tests to assess the different cognitive domains. The CogState Brief Battery computerised test (http://cogstate.com/) will be administered to assess cognitive function including psychomotor function, attention, learning, reaction time, processing speed, visual attention and working memory [81, 82]. The CogState battery involves five computerised tests (Groton maze, detection task, identification task, one card learning task, one back task) conducted in a quiet environment, with scripted instructions and a practice attempt prior to completing each task.

The Rey Auditory Verbal Learning Test will be administered to assess memory and learning [83]. A list of 15 common words is read to the participant five times, with the participant asked to immediately recall as many words as possible following each recital. An interference list is then presented, after which the participant must recall words from the original list. Following a 20-min delay, during which other non-verbal tests are conducted, the participant is asked to recall the original list again. Finally, the participant will be asked to visually identify the words from the original list from a list of 50 words. Participants are scored on the total number of words recalled in trials 1–5, total number recalled after interference, loss after interference number (trial 5 minus trial 2) and long-delay free recall.

The Trail Making Test (Parts A and B) will be administered to assess executive function [84]. Participants will be instructed to accurately draw lines to connect circled numbers in sequential order as fast as possible (Part A). Participants will then be instructed to draw lines to connect circled numbers and letters in an alternating numeric and alphabetic order (Part B).

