### Sample size calculation

The sample size calculations are based on our previous research in healthy and ADT-treated men. The mean (standard deviation (SD)) annual loss in femoral neck, hip and spine BMD in ADT-treated men was 3.0% (4.5), 2.6% (2.8) and 3.9% (3.0), respectively [14]. Our previous exercise trials in healthy older men have shown that 12 months of training can increase spine aBMD by 1.5–2.0% (SD 2.9) and hip aBMD by 1.2–1.8% (SD 2.8) [39, 55]. We estimate a conservative net difference in aBMD in favour of the intervention of ~ 3.5–4.0% at the hip and spine. Based on these estimates, 29 men in each group will provide 90% power (*P* < 0.05, two-tailed) to detect a difference of this magnitude (assuming a SD of 4.0). A net benefit of this magnitude is clinically relevant as there is evidence that a 1–2% gain in aBMD translates into a 7–14% reduction in fracture risk [36, 93]. For pQCT bone measures, radial and tibial cortical area decreased by 11.5% (8.8) and 12.5% (7.4), respectively, over 12 months in ADT-treated men [14]. While few long-term trials have examined the effect of exercise training on pQCT bone geometry in older men, several intervention trials in older adults have shown that a targeted, weight-bearing, impact-exercise programme can have beneficial effects on cortical bone [94, 95]. Assuming that the proposed intervention can half the rate of loss in cortical area, we estimate that we will require 39 men per group (SD 8.0; 90% power, two-tailed, *P* < 0.05). Based on a previous study and a meta-analysis showing that ADT is associated with an average 7.7% gain in fat and a 2.8% loss in lean mass over 3–12 months [96, 97], and that exercise training can prevent the gain in FM and increase (1–5%) or preserve LBM relative to usual care in men on ADT [30, 32], we estimate a sample size of 24–32 in each group will be required to observe a preservation in LBM and FM in the intervention group vs. usual care (90% power, two-tailed, *P* < 0.05). Assuming a conservatively projected 30% dropout, an estimated sample size of 51 men per group (102 in total) will be required. Based on previous studies in ADT-treated men focussing on a number of our secondary outcomes [32, 37, 98], we estimate that we will have sufficient power (80–90%, *P* < 0.05, two-tailed) to detect the following intervention effects: 20–40% for muscle strength; 8–22% for functional capacity; 4 points for fatigue (FACT-F), 15% for fasting plasma glucose and 14% for serum IL-6 and 20% for CRP. We will also have sufficient sample to detect a clinically meaningful difference of 0.5 SD in the Assessment of Quality of Life 8D questionnaire (AQoL-8D) and 9 points on the FACT-P (disease-specific QoL).

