
### Statistical analysis

Primary analyses will be conducted on an intention-to-treat basis using STATA statistical software (STATA, College Station, TX, USA). Per-protocol analysis will also be performed by including all participants who are at least 66% compliant to the exercise (two of three sessions per week) and 80% compliant to taking the supplements. Initially, descriptive statistics will be computed to compare the intervention and usual-care groups on background variables and baseline measures. All data will be screened for outliers and the normality of the distribution of all data will be assessed using Kolmogorov-Smirnov tests, with skewed data log transformed prior to analysis. Linear mixed models with random effects will be used to evaluate the effects of the intervention compared to usual control. Potential covariates to be included will be: age, duration of ADT use, other chronic conditions, change in medication and change in habitual physical activity or diet. Where possible, we will obtain endpoint measures from all withdrawals and include all randomised subjects in the final analysis. For participants who are lost to follow-up, missing data will be handled with multiple imputation, with subsequent sensitivity analyses to evaluate the effect of potential non-random attrition. Baseline measures and changes in outcome variables will be presented as means ± SD or 95% confidence intervals. A significance level of *P* < 0.05 will be adopted for all statistical tests.

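### One rule for every outcome (test the raw data for normality, log whatever is skewed) checks the wrong quantity for a mixed model and does not work for some secondary scores

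*Protocol article*

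**What the plan says.** The Statistical analysis section sets one rule for all variables: "the normality of the distribution of all data will be assessed using Kolmogorov-Smirnov tests, with skewed data log transformed prior to analysis". The model named next is a mixed model: "Linear mixed models with random effects will be used to evaluate the effects of the intervention compared to usual control". Results are to be shown on the measured scale: "Baseline measures and changes in outcome variables will be presented as means ± SD or 95% confidence intervals".

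Other sections define the outcomes that this rule would meet:
- Primary and secondary outcome measures: "The primary outcome for this study will be changes in proximal femur and lumbar spine aBMD".
- Cognitive function lists a verbal-learning score described as "loss after interference number (trial 5 minus trial 2".
- Functional capacity describes the Berg Balance Scale: "The scores of the 14 tasks are summed to produce a total score ranging from 0 to 56 points". Higher is better.
- Sample size calculation gives the detectable effect for fatigue as "4 points for fatigue (FACT-F" and for the FACT-P as 9 points. For IL-6 and CRP it gives percentages (14% and 20%).

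**The concern.** A linear mixed model makes its normality assumption about residuals and random effects. A test on the raw distribution of each variable does not check that assumption. The rule then uses the test result to choose between two scales, so whether an effect is a difference or a ratio depends on the trial's own data.

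The log is also not a general remedy for skew. It needs positive values, and it corrects right skew only. The listed outcomes include a difference score and a bounded score with a ceiling, and for these the prescribed step either cannot be carried out or makes the shape worse. At stake are the scale, interpretability and handling of several secondary outcomes.

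**Working it through.** **The plan's own figure.** The normality sentence contains no figure. The primary sample size (difference 3.5%, SD 4.0, 90% power, two-sided 0.05) is n = 2(1.960 + 1.282)² × 4.0² / 3.5² = 2 × 10.51 × 16 / 12.25 = 27.5, so 28 per group. The t-distribution version gives 28.4, so 29, as stated. Nothing below changes it.

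**Inputs.** N = 102 (51 per group) is from Sample size calculation. All distribution shapes below are assumptions, because the article gives none. The main rates use 1,000 to 3,000 simulated samples.

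**1. Quantity tested.** Two equal subgroups with perfectly normal residuals were pooled and tested raw. The uncorrected test rejected in 0%, 1% and 43% of runs when the subgroup means were 2, 3 and 4 SD apart. The wrong quantity is tested, but this alone changes the decision only when there is large structure in the data.

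**2. Test version.** The statistic is D = max |Fₙ(x) − Φ((x − x̄)/s)|. Standard Kolmogorov-Smirnov critical values assume a known mean and SD; the Lilliefors version corrects for estimating them. The article does not say which is meant. Share of samples flagged at n = 102:

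| Data | Uncorrected | Lilliefors |
|---|---|---|
| Normal | 0.0% | 4.4% |
| Lognormal, log-SD 0.3 | about 6% | about 60% |
| Lognormal, log-SD 0.5 | about 43% | about 95% |

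The same moderately skewed outcome could therefore go to different scales according to a software default.

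**3. Difference score.** Assume trial 5 has mean 11, trial 2 has mean 7.5, both have SD 2.3, and the two are independent. The difference has mean 3.5 and SD √2 × 2.3 = 3.25. With a continuity correction, P(difference ≤ 0) = Φ((0.5 − 3.5)/3.25) = Φ(−0.92) ≈ 0.18, and simulation also gives 18%. With a correlation of 0.5 the SD is 2.3 and the share is Φ(−1.30) ≈ 0.10. So roughly 10% to 18% of values would have no logarithm. As the article describes the test, trial 2 comes before the interference list, so the definition itself deserves a check. Whichever recall is meant, the score remains a difference.

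**4. Ceiling score.** The log stretches the low end. A drop from 56 to 50 is ln(56/50) = 0.113, and an equal drop from 50 to 44 is ln(50/44) = 0.128. For three assumed ceiling-type 0 to 56 distributions, skewness went from −2.0 to −2.6, from −1.67 to −1.96, and from −1.9 to −2.2. In the second and third the rule triggered in 99.9% to 100% of runs.

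**5. Point scales.** A 4-point effect is a ratio of 34/30 = 1.13 from a baseline of 30, or 44/40 = 1.10 from 40 (illustrative baselines). No single ratio corresponds to the effect used for power.

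**6. Error rates of test-then-log** (uncorrected test, then two-sample t test, 51 per group). Type I error was 0.036 to 0.050. Power for a 0.5 SD latent shift:

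| Assumed shape | Raw | Test-then-log | Always log |
|---|---|---|---|
| Right skew, log-SD 0.4 | 67% | 68% | 70% |
| Right skew, log-SD 0.6 | 66% | 71% | 72% |
| Left skew, milder | 67% | 66% | 63% |
| Left skew, stronger | 63% | 52% | 48% |

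In a separate Berg-like example, power was 69% on either scale.

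**The case against.** The strongest reply is that this is one general sentence in a condensed article, that an analyst would not log a negative or left-skewed score, and that outcome-specific scales and residual plots belong in an analysis plan. Much of that is fair, and the absence of those details is not the complaint. What remains is that the article states a rule, and that the rule covers all data. A later plan must either inherit it or depart from it.

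Four stronger readings are tempting and are not supported:
- *The primary outcome cannot be analysed under this rule because losses are negative changes.* The outcome is worded as a change, but a mixed model on measurements at baseline, 26 and 52 weeks can use bone density levels, which are positive. The text does not show that change scores would be logged.
- *The test is simply too insensitive.* That holds only for the uncorrected version. With the Lilliefors correction, most of the same skew is caught.
- *An unblinded team would choose the scale.* Randomisation and blinding says that participants and testing researchers are unblinded and that DXA and pQCT scans are assessed independently. It says nothing about the analyst. A stated rule also leaves less discretion than none.
- *Log transformation is wrong here.* For positive, right-skewed markers it helps, as the right-skew rows above show.

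**Conclusion.** The point holds as a minor one. The rule tests raw data where the model's assumption concerns residuals, is undefined for the verbal-learning difference score at zero or below, and worsens left skew in a ceiling-type score. If triggered, it also takes the FACT-F and FACT-P off their powered point scale. Which outcomes are flagged turns on an unnamed test version.

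The effect is mainly on secondary outcomes. Bone density is probably little affected, on the assumption that its levels are not strongly skewed. False-positive rates are not inflated and no sample size changes. The power cost was nil or about one percentage point in most shapes tried. The exception was 11 points (63% to 52%) in the more strongly left-skewed assumed shape. No effect on the primary conclusion is shown. The undefined log and the direction of its effect on left skew follow from the mathematics; the percentages rest on assumed distributions.

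**What to change.** Replace the test-then-log sentence with scales named in advance:
- Bone density, the other bone and body-composition outcomes, and the point-scale questionnaires: untransformed.
- Positive, right-skewed markers such as CRP and IL-6 (if assayed): log scale, reported as ratios. This also suits the percentage effects given for them in Sample size calculation.
- Bounded or difference scores, such as the Berg scale and the verbal-learning loss score: untransformed, with robust standard errors or a bootstrap as a sensitivity analysis.

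Check the residuals of the fitted models graphically in place of a normality test on raw data.

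The cost is a few lines of text, with no change to data collection, sample size or participants. The small downside is that scales are committed to before the distributions are seen. Trial status reports that recruitment is continuing, so this can be settled before the final data are available.

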### Randomisation and blinding

Randomisation will be at the level of the individual participant following baseline testing, stratified by age (< 65 or ≥ 65 years) and Body Mass Index (< 30 or ≥ 30 kg/m^2^), using a computer-generated, random number sequence by an independent researcher. Due to limited funding, neither the participants nor researchers involved in the testing will be blinded to the group allocation, with the exception of the DXA and pQCT scans which will be assessed independently. A flow diagram of the study protocol is outlined in Fig. 1.

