### Measurements

All measures will be collected at baseline, 26 and 52 weeks. Additionally, 24-h food recalls will also be administered at 13 and 39 weeks to monitor any habitual fluctuations in dietary factors. With the exception of blood samples, 24-h food recalls and questionnaires, all data will be collected at Deakin University. Blood samples will be collected at an external commercial pathology clinic. The 24-h food recalls will be administered via telephone. Questionnaires will be completed by participants at home prior to each testing sessions (i.e. baseline, 26 and 52 weeks) and checked by the research staff during these face-to-face testing sessions. A summary of the proposed outcome measures is shown in Table 2. All participants will undergo all measures expect those specific to treatment allocation (i.e. compliance to the intervention). All data collected will be in a continuous format, aside from the outcomes from some of the questionnaires, which will be categorical in nature.

**Table 2 Tab2:** Summary of data collection

Variables	Data collection method	Data collection points		
		Baseline	26 weeks	52 weeks
Primary outcome measures				
Areal bone mineral density	DXA proximal femur and lumbar spine	x	x	x
Secondary outcome measures				
Bone structure and strength	pQCT scan at 4% and 66% radial and tibial site	x	x	x
Body composition	DXA total body and regional lean mass, fat mass and % body fat	x	x	x
	pQCT 66% radial and tibial muscle cross-sectional area and muscle density	x	x	x
Muscle strength	Chest press, leg press and seated row	x	x	x
	Grip strength	x	x	x
Functional capacity	30-s sit-to-stand	x	x	x
	Timed-up-and-go with cognitive task	x	x	x
	Four-square step test	x	x	x
	Berg balance scale	x	x	x
	Four-metre usual walk	x	x	x
	400-metre walk	x	x	x
Biochemistry and lipids	Overnight, fasted serum and plasma collection	x	x	x
Inflammatory markers	Overnight, fasted serum and plasma collection	x	x	x
Blood pressure	Automated measurement	x	x	x
Cognitive function	CogState Brief Battery computerised tests	x	x	x
	Rey Auditory Verbal Learning Test	x	x	x
	Trail Making Test (Part A and B)	x	x	x
	Digit Span Test	x	x	x
	National Adult Reading Test	x		
Health-related quality of life, fatigue and mood	Functional Assessment of Cancer Therapy-Fatigue questionnaire	x	x	x
	Functional Assessment of Cancer Therapy-Prostate questionnaire	x	x	x
	Assessment of Quality of Life 8D questionnaire	x	x	x
	Geriatric Depression Scale questionnaire	x	x	x

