#### Habitual physical activity

The Community Healthy Activities Model Programme for Seniors physical activity questionnaire will be used to assess participation in a comprehensive list of low, moderate and vigorous physical activities [92]. Participants will document the frequency and duration of their participation in a ‘typical week’ of the preceding 4 weeks. The results will be reported as estimated kilojoules per week spent in moderate- to high-intensity activities and hours per week spent undertaking weight-bearing exercise.

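### Change in activity, diet and medication after randomisation are listed as potential covariates for the intention-to-treat model; if they enter it, it no longer estimates the total effect of the programme

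*Protocol article*

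**What the plan says.** The Statistical analysis section of the protocol article states that "Primary analyses will be conducted on an intention-to-treat basis". It then gives the model: "Linear mixed models with random effects will be used to evaluate the effects of the intervention compared to usual control". The next sentence lists the potential covariates: "age, duration of ADT use, other chronic conditions, change in medication and change in habitual physical activity or diet". Nothing in the section confines the change variables to a secondary, sensitivity or mediation analysis.

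The timing is given elsewhere. Under Randomisation and blinding: "Randomisation will be at the level of the individual participant following baseline testing". Under Measurements: "All measures will be collected at baseline, 26 and 52 weeks". Diet is also measured between those visits: "24-h food recalls will also be administered at 13 and 39 weeks to monitor any habitual fluctuations in dietary factors".

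The Habitual physical activity section describes a questionnaire on a wide range of activities over a recent typical week. Of its scoring it says: "The results will be reported as estimated kilojoules per week spent in moderate- to high-intensity activities and hours per week spent undertaking weight-bearing exercise". Neither that section nor the Diet section says whether programme sessions or supplement sachets are left out of these measures.

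**The concern.** An intention-to-treat comparison should estimate what being allocated to the programme does to bone density, by whatever route. The intervention is supervised and home exercise plus a daily protein, calcium and vitamin D supplement. Change in activity and change in diet are therefore among the first things allocation could move. Holding them constant asks a different question: what the programme does beyond its effect on activity and diet. It can also introduce confounding, because men who change their activity or diet differ in other ways that bear on bone.

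Change in medication needs a separate argument. The intervention does not act through it. But drug starts come after randomisation, participants know their allocation, and a prescription may follow observed bone loss. The article's Discussion says that bisphosphonates prevent bone loss under ADT, so such starts bear directly on the primary outcome.

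At stake is the primary effect estimate. A programme that works could be reported as weaker than it is, or in some circumstances as stronger.

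**Working it through.** **Timing.** Baseline testing comes first, then randomisation, then measurement at 26 and 52 weeks (diet also at 13 and 39 weeks). Any change from baseline in activity, diet or medication is therefore a post-randomisation variable. Age is not. ADT duration and chronic conditions are not either, if taken as they stand at baseline.

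**The plan's own figure.** Inputs from Sample size calculation: difference 3.5% (lower end of 3.5–4.0%), SD 4.0, two-sided 0.05, 90% power. The normal approximation gives 28 per group and the exact two-sample t calculation gives 29, with power 90.6%. The stated 29 reproduces, and this point does not dispute it.

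**Unadjusted power.** 51 per group less 30% dropout is 51 × 0.70 = 35.7, taken as 36. The standard error is 4.0 × √(2/36) = 0.943, and 3.5/0.943 = 3.71. Power is about 96%.

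**With one post-randomisation covariate.** The mediated share and the covariate–arm correlation r are assumptions; the article gives neither. Scale the covariate to within-arm SD 1 and keep the total within-arm SD of the outcome at 4.0.

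- Shift of the covariate between arms: a = 2r/√(1 − r²).
- Slope of outcome on covariate: b = share × 3.5/a.
- Expected adjusted estimate: 3.5 − a·b = 3.5 × (1 − share).
- Residual SD: √(16 − b²), because a covariate that carries effect also explains outcome variance.
- Standard error: residual SD × √(2/36)/√(1 − r²).

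| Share | r | a | b | Residual SD | SE | Estimate | Power |
|---|---|---|---|---|---|---|---|
| 25% | 0.3 | 0.629 | 1.391 | 3.750 | 0.927 | 2.625 | 80% |
| 25% | 0.5 | 1.155 | 0.758 | 3.928 | 1.069 | 2.625 | 68% |
| 25% | 0.6 | 1.500 | 0.583 | 3.957 | 1.166 | 2.625 | 60% |
| 50% | 0.3 | 0.629 | 2.782 | 2.874 | 0.710 | 1.75 | 68% |
| 50% | 0.5 | 1.155 | 1.516 | 3.702 | 1.007 | 1.75 | 40% |
| 50% | 0.6 | 1.500 | 1.167 | 3.826 | 1.127 | 1.75 | 33% |

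**Direction.** A regression simulation (36 per arm, 3,000 replicates, true total effect 3.5) covered four assumed situations:

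- Half the effect runs through the covariate (a = 1, b = 1.75): adjusted estimate 1.73, power 44%.
- The same, plus a common cause of covariate and outcome: estimate 1.18, power 28%.
- Activity outside the programme falls in the intervention arm (a = −0.5, b = 1.0): expected 3.5 + 0.5 = 4.0, simulated 3.99. This bias is away from no effect.
- The covariate is unaffected by arm: estimate 3.50, no bias.

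**The case against.** The list is headed as potential covariates. The article does not say which will enter which model, or whether an unadjusted estimate will also be given, and an analysis plan not shown here may settle this. That stands, and it makes the bias conditional. It does not remove the problem: the article attaches these variables to the models that evaluate the intervention and offers no other role for them, and the quantity estimated depends on whether they go in.

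The word habitual may mean behaviour outside the programme. Attendance and supplement intake are recorded separately under Compliance, which fits that reading. This also stands as a possibility. A reader might infer that men in the intervention arm will simply report their training sessions in the questionnaire, so that the estimate must shrink. The documents do not support that certainty, because no section says whether sessions or sachets are counted. But the narrower meaning does not make the covariates safe: outside activity and diet can also respond to allocation, and compensation would push the estimate the other way.

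A reader might also treat medication as a third route by which the programme works. Nothing in the article presents it so. The case against adjusting for it rests only on its being a post-randomisation variable that may respond to allocation or to bone loss.

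Finally, the power figures rest on assumed inputs. That is right; they illustrate the problem and do not bound it.

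**Conclusion.** The point holds in conditional form. The protocol article lists three post-randomisation variables as potential covariates for the intention-to-treat models, and at least two of them, activity and diet, can be altered directly by the intervention. If they enter the primary model, it does not estimate the total effect of the programme and can be biased. Attenuation follows if the measures capture the programme. Inflation is possible if they capture only outside behaviour and that behaviour falls in the intervention arm. There is no bias from this source if the variables are left out, or if neither allocation nor its consequences affect them. The documents do not settle the direction.

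For scale only, the table's assumptions (one mediating covariate, r from 0.3 to 0.6, total within-arm SD 4.0) take a 3.5% effect with about 96% power down to 2.6% with 60–80% power at a 25% share, or to 1.75% with 33–68% power at a 50% share.

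**What to change.** Delete change in medication and change in habitual physical activity or diet from the covariates of the primary model. Allow baseline variables only: age, ADT duration at baseline and chronic conditions at baseline.

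Report change in activity, diet and medication by arm. If they are used in a model, do so only in a labelled exploratory or mediation analysis, and state there whether programme sessions and sachets count towards the activity and diet measures.

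Keep men who start bone-active drugs in the primary analysis. Any analysis that drops scans taken after such a start conditions on a post-randomisation event, so label it supplementary and do not present it as a randomised comparison.

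The cost is a few lines of analysis wording. No further data or participants are needed, and the article's Trial status section says recruitment is still under way.
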